**Methods/Design:**

The study, conducted in the Hunter region of New South Wales, Australia, employs a cluster randomised controlled trial design. Two hundred parents from 15 randomly selected preschools will be randomised to receive the intervention, which consists of print resources and four weekly 30-minute telephone support calls delivered by trained telephone interviewers. The calls will assist parents to increase the availability and accessibility of fruit and vegetables in the home, create supportive family eating routines and role-model fruit and vegetable consumption. A further two hundred parents will be randomly allocated to the control group and will receive printed nutrition information only. The primary outcome of the trial will be the change in the child's consumption of fruit and vegetables as measured by the fruit and vegetable subscale of the Children's Dietary Questionnaire. Pre-intervention and post-intervention parent surveys will be administered over the telephone. Baseline surveys will occur one to two weeks prior to intervention delivery, with follow-up data collection calls occurring two, six, 12 and 18 months following baseline data collection.

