### Study Design

#### Overview of study design

The study employs a cluster randomised design, as outlined in Figure 1. The research will be reported in accordance with the requirements of the CONSORT statement [27]. Parents of 3- to 5-year-old children attending randomly selected preschools in the Hunter region of New South Wales, Australia, are being approached to participate. Preschools will be randomised to either control or intervention groups using a random number function in Microsoft Excel. Parents of children attending preschools allocated to the intervention group will receive a series of instructional resources and four 30-minute telephone calls delivered weekly by trained telephone interviewers. Parents of children attending preschools allocated to the control group will receive a readily available nutrition resource published by the Australian Government [28]. To assess the efficacy of the intervention, surveys will be conducted with parents *via *Computer Assisted Telephone Interview (CATI) at baseline (occurring one to two weeks prior to commencement of intervention delivery) and two, six, 12 and 18 months following baseline data collection.

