### Control Group

Participants allocated to the control group will receive a 22-page booklet, 'The Australian Guide to Healthy Eating: Background information for consumers' [28]. This is a national food guide published by the Australian Government Department of Health and Ageing. This publication will be posted to parents' residential addresses following completion of the baseline survey.

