#### Sample size

A sample size of approximately 300 participants (150 per group) at the 18-month follow-up will allow a detectable difference between intervention and control groups of 1.27 on the fruit and vegetable subscale of the Children's Dietary Questionnaire, with 80% power at the 0.05 significance level. This sample size accounts for the effect of clustering by assuming an interclass correlation coefficient of 0.03 (unpublished data from the *Good for Kids *program) and assumes 10 participants per preschool remain at the 18-month follow-up (as explained below).

Four hundred participants will be required to be recruited at baseline to achieve the desired sample of 300 at the 18 month follow-up. Based on preschools caring for an average of 27 children each day [34], and assuming children attend preschool for an average of 2.8 days per week (i.e. 17 hours over 6-hour long days), it is expected that up to 48 parents of children, on average, will be eligible to participate in the trial from each consenting preschool. A parent participation rate of 30% [19] will yield approximately 14 parents per preschool at baseline, of whom 10 will remain at 18 months, assuming a 25% attrition rate [63]. It is thus estimated that 30 preschools will be required to generate a sample of 300 parents at the conclusion of the trial.

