#### Statistical analysis: primary outcome

All statistical analyses will be performed with SAS (version 9.2 or later) statistical software.

To assess the initial impact of the intervention and the extent to which any intervention effect is maintained in the longer term, the primary outcome analyses for the trial will be conducted on participant scores on the fruit and vegetable subscale of the Children's Dietary Questionnaire collected at the two-month and 18-month follow-up time periods. For the primary outcome analyses, an alpha value of 0.05 will be utilised to determine statistical significance.

Outcome data will be analysed using general estimating equations based on the intention-to-treat principle, where participants are analysed based on the groups to which they were allocated, regardless of the treatment type or exposure that they actually received [64]. General estimating equation models will account for any clustering effect of preschools. To ensure the results of the primary analysis are robust against the missing data assumption of the general estimating equation, a sensitivity analysis will be performed whereby participants' observations at baseline will be used as a substitute for subsequent missing data. A per-protocol analysis will also be conducted whereby outcome data will only be included in analyses if participants received and completed all four telephone support calls. Conducting both intention-to-treat and per-protocol analyses is recommended when assessing trial outcomes [64].

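### The supplementary per-protocol rule, as written, admits no control participant; read as a filter on the intervention arm only, it is open to selection bias

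*Protocol article*

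**What the plan says.** Three places in the protocol article bear on this point.

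- **Statistical analysis: primary outcome.** The main analysis is by intention to treat, in which "participants are analysed based on the groups to which they were allocated, regardless of the treatment type or exposure that they actually received". A per-protocol analysis is then added, in which "outcome data will only be included in analyses if participants received and completed all four telephone support calls". The reason given is that "Conducting both intention-to-treat and per-protocol analyses is recommended when assessing trial outcomes".
- **Control arm.** The abstract says that control parents "will receive printed nutrition information only". The Control Group section says the same in more detail: "Participants allocated to the control group will receive a 22-page booklet".
- **Intervention arm.** Under Overview of study design, parents at intervention preschools "will receive a series of instructional resources and four 30-minute telephone calls delivered weekly by trained telephone interviewers". Under Intervention resources, every intervention parent is also mailed a kit (workbook, meal planners and cookbook) after the baseline survey.

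The article gives no adherence criterion for controls. It describes no adjustment for selection into call completion, and nothing in it marks the per-protocol comparison as non-randomised.

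**The concern.** The preceding sentence on intention to treat uses the word participants for both arms, and the per-protocol sentence uses the same word without limiting it. Followed to the letter, it asks control parents to have completed calls that they were never offered. The article states an inclusion rule and the rule fails when applied, so this is more than a detail left to an analysis plan.

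The obvious repair is to filter only the intervention arm, but this has its own difficulty. Completing four calls of about 30 minutes is behaviour that occurs after randomisation, and it has no counterpart among controls. The Background section links poor attendance and drop-out in parent programmes to work schedules, lack of interest and child illness, though it hopes that telephone delivery will ease such barriers. If completers would have scored differently from non-completers without any calls, the comparison mixes that difference with the effect of the intervention. The result would be reported beside the intention-to-treat estimate under the primary outcome, where a reader could give it similar standing.

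**Working it through.** **Who can meet the rule as written**

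- Intervention arm: 200 allocated, all offered four calls, so those who complete all four qualify.
- Control arm: 200 allocated, none offered a call, so 0 of 200 qualify at randomisation and 0 of about 150 at 18 months.
- With an empty control set, no between-group effect can be estimated.

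**The plan's own figures**

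The Sample size section gives "A sample size of approximately 300 participants (150 per group) at the 18-month follow-up", a detectable difference of 1.27 points, 80% power, alpha 0.05, an intraclass correlation of 0.03, 10 participants per preschool and 25% attrition.

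- Baseline sample: 300 / (1 − 0.25) = 400, as stated.
- Design effect: 1 + (10 − 1) × 0.03 = 1.27. That this equals the detectable difference is coincidence.
- Effective sample per arm: 150 / 1.27 = 118.1.
- No standard deviation is stated, so the 300 cannot be checked independently. Solving for the SD with a two-sided test: 1.27 / [(1.960 + 0.842) × √(2 / 118.1)] = 3.48 points. A one-sided test would imply 3.93. I use 3.48 only to set a scale.

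**Bias if only the intervention arm is filtered**

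Let c be the share of intervention parents who complete four calls. Let g be the gap between would-be completers and non-completers in the untreated outcome as analysed, in SD units. If the intervention has no effect:

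bias = (1 − c) × g × SD

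Neither c nor g is in the document. I assume c from 0.6 to 0.9 and g from 0 to 0.5. The standard error is SD × √{[1 + (10c − 1) × 0.03] / (150c) + 1.27 / 150}. Type I error is for a nominal two-sided 5% test at 18 months.

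| c | g | Bias (points) | Share of 1.27 | Type I error |
|---|---|---|---|---|
| any | 0 | 0 | 0% | 5.0% |
| 0.9 | 0.3 | 0.10 | 8% | 5.6% |
| 0.8 | 0.3 | 0.21 | 16% | 7.3% |
| 0.7 | 0.3 | 0.31 | 25% | 9.8% |
| 0.6 | 0.5 | 0.70 | 55% | 27.9% |

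For example, with c = 0.8 and g = 0.3: 0.2 × 0.3 × 3.48 = 0.21, and 0.21 / 1.27 is about 16%. A negative g reverses the sign of the bias.

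**Why an instrumental-variable estimate is not a clean replacement**

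Let τ be the effect in four-call completers and κ the effect, in those who do not complete, of the mailed kit and any one to three calls. The intention-to-treat effect is then cτ + (1 − c)κ. Dividing by c gives τ + [(1 − c) / c] × κ. The excess over τ is 0.11κ at c = 0.9, 0.25κ at c = 0.8 and 0.67κ at c = 0.6. It vanishes only if non-completers gain nothing.

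**The case against.** The best defence is that per-protocol means adherence to the assigned treatment. Four calls are assigned only to the intervention arm, so a sensible analyst would filter that arm and keep the controls. An analysis with no comparator could not be carried out unnoticed. The text is a condensed article, per-protocol is only an addition to intention to treat, and any per-protocol set that drops non-adherers gives up the protection of randomisation. Much of this stands: filtering one arm is the probable intent, and neither the main analysis nor the sample size depends on the rule. It does not rescue the wording, because the article states a rule that excludes every control and nothing else in it says how controls enter.

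A reader might go further and infer that the per-protocol result must favour the intervention, because motivated parents have children who already eat better. The document does not support that. Its primary outcome is change in intake, and the same survey is given at baseline and follow-up. If change is what is modelled, a stable difference in level largely cancels, and only a difference in untreated change would matter. The analysis section speaks of scores, so the point is not settled, but neither the direction nor the size of bias can be read from the text.

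**Conclusion.** The point holds in two parts of different strength. That the literal rule leaves no controls follows from the text with no assumptions. That the one-arm reading is open to selection bias also holds, but how much bias there would be is unknown. The range of 0 to 0.70 points (0% to 55% of the detectable difference), with type I error from 5.0% to about 28%, rests on assumed completion, an assumed completer gap that is not negative, and a back-calculated SD. The mid case is 0.21 points and 7.3%. If completion is unrelated to prognosis, the bias is zero.

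A reader might infer that the trial's main conclusion is at risk. It is not: the intention-to-treat analysis keeps everyone in the allocated group and is untouched. The defect lies in a supplementary analysis and is of moderate to minor weight. Nor does the document support discarding the per-protocol analysis for an all-four-calls instrumental-variable estimate, since the kit goes to every intervention parent and partial call completion is possible.

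**What to change.** Amend the per-protocol paragraph to say that:

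1. the four-call requirement applies to the intervention arm only, and all control participants with outcome data are included;
2. the comparison is adjusted for baseline score and the socio-economic stratum used in the randomisation;
3. the result is a non-randomised comparison, secondary to intention to treat.

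In addition, and not as a substitute, report a complier-average causal effect estimate with allocation as the instrument and standard errors clustered by preschool. State the exclusion restriction, and say that the estimate overstates the effect in completers if the kit or one to three calls help those who do not complete. Repeating it with any call, or the number of calls, as the exposure would show how far the answer depends on that assumption. These versions relax the restriction for partial completion but not for the kit.

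The cost is a few sentences and a little more analysis. The baseline survey and the call outcomes logged by the telephone interview system already supply the data. Baseline adjustment reduces selection bias but cannot be relied on to remove it. The complier-average estimate will have a wider confidence interval than a simple per-protocol comparison.

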## Discussion

To the authors' knowledge, this is the first randomised controlled trial to evaluate a telephone-based parent intervention to increase the fruit and vegetable intake of preschool-aged children. The intervention has been developed to maximise the likelihood of having a positive effect on fruit and vegetable consumption through the use of a relevant conceptual model during intervention development, and employing specific behaviour change strategies to target characteristics of the home food environment known to be associated with increased fruit and vegetable intake.

The study demonstrates many strengths: the experimental randomised design; the implementation of procedures to reduce potential threats to internal validity, such as the blinding of data collection interviewers and computer-based randomisation of groups undertaken by an independent statistician; the use of an outcome measure with established validity and reliability; and the recruitment of study participants from a setting which most 4-year-old children attend on multiple days of the week. If found to be effective, an intervention of this intensity, utilising trained staff rather than experienced health professionals, is considered to have the potential to be implemented on a community-wide basis, as currently exists for adult risk behaviours [20].

## Conclusion

This manuscript provides a comprehensive description of the study methods to be employed as part of a randomised controlled trial of a telephone-based parent intervention to increase the fruit and vegetable intake of children aged 3 to 5 years. The successful implementation of this trial will provide strong evidence on which to base judgements regarding the efficacy of this intervention approach.
